#### Sample size

Power calculations are made relative to the primary endpoint, which is the number of admissions after 6 months. A previous study focusing on a systematic nutritional effort in connection with discharge showed a reduction in the number of admissions (28% in the intervention group and 52% in the control group) during the first 6 months after discharge [2]. By accumulating these numbers with a significance level of 0.05% and a power of 0.80, there must be 64 older patients in each group, a total of 128, to ensure enough power to assess the older medical population. To investigate if patients with cancer also could benefit from the intervention, it is further desired to add a total of 40 extra patients with a cancer diagnosis. However, because it is expected that patients with cancer will be readmitted often, we want to be able to remove these patients from the analyses and still have sufficient power to assess the effect on older medical patients. To also account for dropouts, the goal is 100 patients in each group, for a total of 200 participants.

### Study interventions

The intervention procedure is presented in Table 1 and described in detail below.

#### Intervention group

The intervention group is offered individualized dietary counseling delivered by a research dietitian affiliated with the hospital. The dietitian will perform a comprehensive individualized nutritional assessment to identify the cause of malnutrition, such as lack of appetite, nausea, swallowing problems, polypharmacy, mouth and dental problems, or obstipation. However, the focus is on the dietary intake, activity level, and weight of each participant as a basis for developing a nutrition plan consistent with estimated nutritional requirements and nutritional rehabilitation goals. Specific focus will be placed on optimizing the intake of protein during the day and on the importance of additional strength training. The individualized nutrition plan is delivered together with nutritional information provided on a handout sheet. The counseling will take place in connection with the discharge of the patient. The dietary counseling is standardized so that each session at least contains guidance for meal distribution and meal sizes, counseling in energy- and protein-rich meals and drinks, recommendations for ONSs, a recommendation of protein-rich drinks before bedtime to achieve the maximal anabolic response, the nutrition plan, and recommendation of daily intake of multivitamin tablet.

The individualized nutritional plan, which includes an assessment of nutritional problems, a description of the nutritional therapy started in the hospital, the dietary plan, and finally recommendations for handling the nutritional situation after discharge will be communicated to the municipality (i.e., the general practitioner and the home care if applicable). The purpose of this is that the municipality health care personnel should support the nutritional interventions initiated by the hospital dietitian. If the patient experiences a worsening that requires intervention (e.g., massive weight loss during the intervention period), the municipality will be contacted again.

On day 4 after discharge, the patient will be called by the hospital dietitian for the second individual dietary counseling. The purpose of this is to clarify any additional questions, provide further guidance in the handout nutritional information material, and adjust the nutritional plan if necessary. A need for adjustment of the nutritional plan is based on a questionnaire, where compliance with the nutritional plan, assessment of energy and protein intake in relation to needs, appetite (Simplified Nutritional Appetite Questionnaire [SNAQ]; see “Outcome assessments” section), frequency of strength training, experience of daily diet, use of ONSs, and eventual involvement of home care and startup of home-delivered meals are assessed. Thirty days after discharge, the patient is contacted again by the hospital dietitian for phone-based individual dietary counseling. Again, the purpose is to clarify any additional questions and eventually adjust the nutritional plan on the basis of a questionnaire. The participants and the participants’ relatives are encouraged to contact the hospital dietitian whenever needed and also after day 30.

The intervention group will receive a food package to cover the first 24 h after discharge. The food package is produced by the Nutritional Unit, Herlev Gentofte Hospital, and is based on recipes developed in former projects [17, 22, 23].

The dishes in the food package will consist of energy- and protein-rich main and in-between meals as well as energy- and protein-rich drinks. The food is either naturally rich in energy and protein, enriched with naturally energy-tight ingredients, and/or industrially produced dairy protein powder, when enrichment with natural protein sources is not possible. The daily diet is available in three different energy and protein levels to best cover the patients’ individual needs. The levels of the daily diet start at 6500 kJ and 65 g of protein; the second level is 7500 kJ and 75 g of protein; and the third level is 8500 kJ and 85 g. If needed, the dietitians can further individualize the diet to increase either energy or protein or both.

Food and drink are provided for free to the patient. The first 50 patients in the intervention group will be provided with a questionnaire in which they are asked to note what they think about the food delivered, how the food has been to handle in the home, and what price they might possibly pay for the food delivered.

The intervention group will also receive a free “goodie bag” containing samples of energy- and protein-rich milk products for use in the week after admission. The purpose is for the patients to have the opportunity to taste different flavors. The intervention group will be recommended to take an energy- and protein-rich product just before bedtime for 16 weeks. The participants must purchase these at their own expense. After 16 weeks, the intervention group receives a home visit by research assistants to collect outcome data. A short dietetic counseling session is held if required.

#### Control group

The control group will receive standard care at discharge, which means they follow the standard procedure for discharge, which is different from ward to ward and according to diagnosis. It is the treating ward that decides what standard care entails, such as increased home care or follow-up by the local physician. It does not include dietary counseling or a food package. After 112 days, the control group also receives a home visit to collect data, but no dietetic counseling is performed.

### Outcome assessments

The intervention will last 16 weeks (see Table 1). Assessments of the participants will be conducted by the research dietitian at baseline before randomization. After 16 weeks, data are collected by a research assistant who is not a part of the intervention. In addition, information will be collected from the hospital patient register at baseline and after 4, 30, and 112 days (Fig. 1 shows the SPIRIT figure). Data are collected using specific forms on paper created by the investigators. The researchers will meet regularly to monitor the trial process and check, for example, to see how recruitment is progressing and whether all outcome data are collected according to the protocol to ensure data quality.

Primary and secondary outcomes are described in detail below.

#### Primary outcome

##### Admissions after 6 months

Nonplanned admissions within 6 months will be assessed using data from the hospital patient register, where the number of admissions can be found. The prevalence in each group will be calculated. The length of stay at each admission is also recorded and averaged for the two groups.

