#### Secondary outcomes

##### Readmissions

Readmissions, defined as admission within 30 days postdischarge, will be assessed by data from the hospital patient register, where the number can be found. The prevalence in each group will be calculated. The length of stay at each readmission is also recorded and averaged for the two groups.

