##### Admissions after 112 days

Nonplanned admissions within the intervention period will be assessed by data from the hospital patient register, where the number of admissions can be found. The prevalence in each group will be calculated and averaged for the two groups.

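### Length of stay is averaged per admission, which is not a randomised comparison, and the 30-day readmission definition lacks the nonplanned restriction used at 112 days and 6 months

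*Protocol article*

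**What the plan says.** Three outcomes in the protocol article count hospital admissions from the same register.

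- *Admissions after 6 months* (primary): "Nonplanned admissions within 6 months will be assessed using data from the hospital patient register". The share of patients admitted is calculated in each group, and then "The length of stay at each admission is also recorded and averaged for the two groups".
- *Readmissions* (secondary): "Readmissions, defined as admission within 30 days postdischarge, will be assessed by data from the hospital patient register". The share is again calculated, and "The length of stay at each readmission is also recorded and averaged for the two groups".
- *Admissions after 112 days* (secondary): "Nonplanned admissions within the intervention period will be assessed by data from the hospital patient register". No length of stay is mentioned here.

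Total hospital days per randomised patient appear nowhere, and the length-of-stay sentences do not say what value a never-admitted patient receives. Mortality is a separate secondary outcome at 30 days, 112 days and 6 months, and is not linked to length of stay. *Data and statistical analysis* lists tests by type of variable and names none for length of stay.

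**The concern.** There are two separate problems.

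**Length of stay.** Read plainly, the unit averaged is the admission. The average is then taken over patients selected by the very event that the intervention should prevent. If it works, the admitted patients in the two arms are no longer comparable, and their mean stay reflects which admissions were avoided as well as how long the remaining ones lasted. The Discussion wants evidence on reducing costly admissions to support cost-effectiveness. Mean stay per admission does not measure hospital use per patient treated.

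**Admission definition.** Two of the three windows are limited to nonplanned admissions and the shortest is not. Followed literally, a scheduled admission on day 20 counts at 30 days but not at 112 days or 6 months, so 30-day prevalence could exceed 112-day prevalence. Admissions that were already scheduled add events to both arms that the intervention is unlikely to prevent. The article gives no reason for the difference.

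**Working it through.** **Step 1. Reproduce the plan's own figure.** *Sample size* gives "28% in the intervention group and 52% in the control group" over 6 months, power 0.80 and 64 per group. With p1 = 0.28, p2 = 0.52, mean 0.40 and two-sided alpha of 5%:

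n = [1.96·√(2·0.40·0.60) + 0.8416·√(0.28·0.72 + 0.52·0.48)]² / 0.24² = 64.2, so 65 per group.

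The arcsine formula gives 63.9, so 64. The figure reproduces, and 28% versus 52% can serve as the plan's own scenario. (The section prints alpha as 0.05%, which would need 154 per group. The analysis section uses p < 0.05. That is a separate matter.)

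**Step 2. Length of stay, equal stays.** Take 100 patients per arm and assume one admission per admitted patient, each of 7 days. The article gives no stay lengths.

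- Per admission: 28·7/28 = 7.0 days (intervention) and 52·7/52 = 7.0 days (control).
- Per randomised patient: 28·7/100 = 1.96 and 52·7/100 = 3.64 days, which is 1 − 1.96/3.64 = 46% fewer.

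The per-admission mean shows none of this difference.

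**Step 3. Length of stay, short stays prevented.** Assume that the 24 avoided admissions would each have lasted s days and that the other 28 last L days in both arms.

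- Control per admission: (24s + 28L)/52. Intervention: L. Difference: 24(L − s)/52.
- Control per randomised patient: (24s + 28L)/100. Intervention: 28L/100. Difference: 24s/100 fewer days with the intervention.

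| s, L (assumed days) | Per admission, intervention vs control | Per randomised patient, intervention vs control |
|---|---|---|
| 2, 8 | 8.0 vs 5.2 | 2.24 vs 2.72 |
| 3, 8 | 8.0 vs 5.7 | 2.24 vs 2.96 |
| 5, 8 | 8.0 vs 6.6 | 2.24 vs 3.44 |
| 2, 10 | 10.0 vs 6.3 | 2.80 vs 3.28 |
| 3, 10 | 10.0 vs 6.8 | 2.80 vs 3.52 |
| 5, 10 | 10.0 vs 7.7 | 2.80 vs 4.00 |

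The sign of the per-admission difference depends only on whether the avoided stays are shorter or longer than the remaining ones. In this scenario days per patient fall whenever admissions are avoided.

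**Step 4. The 30-day definition.** Let p be the nonplanned 30-day risk and q the risk of a planned admission, independent of p and equal in both arms. The risk of any admission is 1 − (1 − p)(1 − q), so the difference between arms is multiplied by (1 − q). With assumed p of 20% (control) and 10% (intervention), and 100 per group:

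| q (assumed) | Control vs intervention | Difference | Power |
|---|---|---|---|
| 0% | 20% vs 10% | 10 points | 0.51 |
| 10% | 28% vs 19% | 9 points | 0.32 |
| 20% | 36% vs 28% | 8 points | 0.23 |
| 30% | 44% vs 37% | 7 points | 0.17 |

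The article supplies neither p nor q, so the table shows only the direction and how sensitive the result is.

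**The case against.** Much can be said for the plan.

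- Length of stay is an add-on to the admission outcomes. It has no heading, hypothesis or named test, and may have been meant as description only. This stands and limits the weight of the point.
- The averaging denominator is not spelled out, and a condensed article may leave it to a document not shown. A per-patient average is therefore not strictly excluded, although the wording points to the admission.
- A reader might infer from Step 3 that the plan would report harm where there is benefit. The documents do not support that. The plan's primary statistic is the share of patients with a nonplanned admission, which in the same scenario is 28% versus 52% and shows the benefit. A reversed length-of-stay mean would be read beside it, and the reversal needs selective prevention of short stays, which is an assumption.
- A reader might also infer that repeat stays of one patient will be analysed as independent. No standard error or model for length of stay is described, so that is conjecture.
- The 30-day definition never says that planned admissions count. The missing word may be a drafting slip. Disseminated cancer is excluded, and the plan wants to be able to analyse without the cancer patients, which may limit the number of scheduled admissions. Even so, recruitment includes oncology and gastrointestinal departments, *Sample size* expects frequent readmission in cancer, and the three definitions differ as printed.
- Hospital days per randomised patient, scored 0 if not admitted, would give an early death without admission the best value. This objection is sound, and the fix has to meet it.

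**Conclusion.** Both parts hold in limited form.

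As worded, the length-of-stay averages at 6 months and 30 days condition on admission and are not randomised comparisons. At the plan's own admission rates, with one admission each and equal 7-day stays, they would show no difference (7.0 versus 7.0 days) while days per randomised patient differ by 3.64 − 1.96 = 1.68. If short stays are selectively prevented, the mean can be longer in the better arm. All stay lengths here are assumed. That the average can mislead does not depend on the values chosen, but the sizes do.

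The 30-day outcome is defined differently from the 112-day and 6-month outcomes, so the windows are not nested and the 30-day contrast can be diluted by an amount that the article does not allow one to estimate.

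The primary endpoint and its sample size are untouched. The point concerns one secondary definition and two ancillary summaries. It should be corrected, but it does not threaten the main result.

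**What to change.** 1. In *Readmissions*, define the outcome as a nonplanned admission within 30 days of discharge, matching the other two windows. Report planned admissions separately by arm.
2. For hospital use, compare total nonplanned hospital days per randomised patient within 30 days, 112 days and 6 months, with 0 for patients not admitted. A mean difference with a bootstrap confidence interval would suit such skewed data, though other methods are defensible.
3. Deal with deaths explicitly: show this result beside mortality for the same window, or use days alive and out of hospital, so that an early death does not score as the best value.
4. Keep stay per admission as a descriptive figure, with the number of admissions and of admitted patients, and without a test between arms.
5. Record the change with a date before the statistician learns the allocation.

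The cost is small. Admissions and stays are already taken from the register, and the split into planned and nonplanned is already needed for the 112-day and 6-month outcomes. The downside is that fewer 30-day events are counted and a little more derivation is needed.

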#### Secondary outcomes

##### Readmissions

Readmissions, defined as admission within 30 days postdischarge, will be assessed by data from the hospital patient register, where the number can be found. The prevalence in each group will be calculated. The length of stay at each readmission is also recorded and averaged for the two groups.

##### Admissions after 112 days

Nonplanned admissions within the intervention period will be assessed by data from the hospital patient register, where the number of admissions can be found. The prevalence in each group will be calculated and averaged for the two groups.

##### Quality of life at baseline and after 16 weeks

Health-related quality of life will be assessed using the EuroQol–5 dimensions–3 levels (EQ-5D-3L). The EQ-5D-3L questionnaire comprises five domains: mobility, self-care, usual activities, pain/discomfort, and anxiety/depression. Each domain has three levels, ranging from no problems to extreme problems. The raw score must be converted to an EQ-5D-3L score. In addition, the participant is asked to record his/her self-rated health on a vertical visual analogue scale where the endpoints are labeled “Best imaginable health state” and “Worst imaginable health state” [26]. Permission to use the questionnaire has been obtained from the EuroQol Research Foundation.

##### Appetite at baseline and after 16 weeks

Appetite will be assessed using the SNAQ. The SNAQ consists of four questions about appetite, taste, satiety, and number of meals. Each question has five possible answers, and the participants are asked to choose the category that reflects their situation. The questionnaire results in a score ranging from 5 to 20. A score ≤ 14 is predictive of 5–10% weight loss [30]. The score for each participant will be recorded at the two time points.

##### Physical performance status at baseline and after 16 weeks

Physical performance status will be assessed by means of the 30-s chair stand. The participants are asked to fold their arms across their chest and to stand up and sit down on a chair without pushing off with their arms as many times as possible for 30 s. The arms may be used for assistance or for safety if needed [10]. The mode of chair stand will be registered, and the number of chair stands for each participant will be recorded at the two time points. An improvement in physical performance will be considered present if a participant no longer needs the arms when doing the test.

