### Data and statistical analysis

The full analysis set will follow the intention-to-treat principle and will include all randomized patients for whom a baseline assessment is conducted, regardless of later temporary or permanent loss to follow-up. Lack of outcome data due to loss to follow-up or if data were unobtainable (i.e., if a patient was readmitted to the hospital and did not want to participate any further) will be treated as missing data and will be excluded from the final analysis. Subgroup comparisons will be made between fully compliant participants (i.e., those who, respectively, do and do not achieve an intake of energy and protein at or above 75% of their estimated requirement).

Descriptive and summary statistics will be used to quantify participants’ characteristics and outcome variables. Nonparametric statistics will be applied whenever nonnormality of the outcomes is detected. Unpaired data will be analyzed by Student’s *t* test or the Mann-Whitney *U* test, and paired data will be analyzed by a paired Student’s *t* test or Wilcoxon signed-rank test as appropriate. For dichotomous variables, difference in proportions will be analyzed by a chi-square test. To detect correlations, Pearson’s or Spearman’s correlation will be used as appropriate. For comparison of tests within the group, general linear models will be used. Two-sided tests of statistical significance will be used in statistical analysis. A *p* value < 0.05 will be considered statistically significant. All analyses will be performed using SAS Enterprise guide 7.1 (SAS Institute, Cary, NC, USA).

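### The chair-stand improvement criterion counts change in one direction only, cannot be met by anyone arm-free at baseline, and is not linked to the stand count

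*Protocol article*

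**What the plan says.** All of this stands in the protocol article, under *Physical performance status at baseline and after 16 weeks*, unless another section is named.

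- The task is to "stand up and sit down on a chair without pushing off with their arms as many times as possible for 30 s".
- Arm use is nevertheless allowed: "The arms may be used for assistance or for safety if needed".
- Both features are kept: "The mode of chair stand will be registered, and the number of chair stands for each participant will be recorded at the two time points".
- One criterion for improvement is given: "An improvement in physical performance will be considered present if a participant no longer needs the arms when doing the test". There is none for worsening, and none for a higher count within the same mode.
- *Data and statistical analysis* adds only general rules. For continuous outcomes: "Unpaired data will be analyzed by Student’s *t* test or the Mann-Whitney *U* test". For binary ones: "For dichotomous variables, difference in proportions will be analyzed by a chi-square test". Neither refers to chair-stand mode.

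**The concern.** The article yields two readouts from one test: a yes/no improvement and a number of stands. Each has a weakness, and nothing says how they fit together.

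The yes/no criterion is one-directional. It credits giving up the arms, ignores starting to need them, and is closed to anyone who begins arm-free. The *Background* cites guidance that nutritional support should lower the risk of functional decline after discharge. Decline prevented is exactly what this criterion cannot show.

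The count can come from either mode, and an assisted stand is an easier task than an unassisted one. If more intervention participants give up the arms, their counts may fall because the task became harder, and a real benefit could look like a loss.

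At stake is the interpretation of a secondary outcome on which the trial hopes to see benefit. The primary endpoint, admissions within 6 months, is not involved.

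**Working it through.** **Is there a figure to reproduce?** No. The article gives no effect size, standard deviation or share of arm users for this outcome. Its sample-size figure concerns admissions and plays no part here. The main check is logical; the numbers below are labelled illustrations.

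**Step 1. Apply both readouts to hypothetical participants.**

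| Baseline | Week 16 | Stated criterion | Change in count |
|---|---|---|---|
| 9 assisted | 5 unassisted | improved | 5 − 9 = −4 |
| 6 unassisted | 12 unassisted | cannot be met | 12 − 6 = +6 |
| 8 unassisted | 8 assisted | not scored | 8 − 8 = 0 |
| 3 assisted | 9 assisted | not met | 9 − 3 = +6 |

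In row 1 the readouts point in opposite directions. In row 2 a doubled count does not register on the criterion. In row 3 neither readout shows the loss.

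**Step 2. The ceiling.** Let q be the share using arms at baseline and c the share of those who later do without. The proportion improved is q × c, so it cannot exceed q. *Inclusion criteria* admit patients from age 50 with planned discharge home, and *Exclusion criteria* remove the permanently bedridden. Some participants can therefore be expected to be arm-free at the start, but the article does not say how many.

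Illustration: 100 per group (the recruitment goal under *Sample size*, with no loss), assumed c = 40% v 20%, two-sided 5%, pooled normal formula for two proportions.

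| q (assumed) | Improved, intervention v control | Power |
|---|---|---|
| 10% | 4% v 2% | about 13% |
| 20% | 8% v 4% | about 22% |
| 30% | 12% v 6% | about 32% |
| 50% | 20% v 10% | about 51% |

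Even a doubling of conversion is hard to detect at these values. The table illustrates the ceiling; it does not estimate this trial's power.

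**Step 3. The count when mode changes.** Suppose a share s moves from assisted to unassisted standing, each with an assumed drop of 3 stands, and nobody else changes. The mean count changes by −3 × s: −0.15 at s = 5%, −0.30 at 10%, −0.60 at 20% and −0.90 at 30%. Every one of those participants is improved by the stated criterion. An excess of such participants in the intervention group would pull the raw comparison against it.

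**The case against.** The strongest reply is that the criterion says *if*, not *only if*. Read beside the sentence on mode and count, it may simply supplement the count: giving up the arms is credited even when the count falls. Row 1 would then be the case the sentence was meant to settle. This reading is fair, and a reader who infers that nothing else can count as improvement goes beyond the text. What remains is that no other criterion is given, and that the one given works in one direction.

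Other stronger readings are also unsupported:

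- *Assisted and unassisted counts will be pooled.* The article does not say so. Mode is registered, and an analysis plan not shown could separate them. What can be said is that no rule links mode and count.
- *Participants arm-free at baseline are discarded.* They are not. They stay in the denominator and their counts are kept, so six rising to twelve is visible in the count.
- *No other information on function is collected.* The chair stand is the only performance test, but the EQ-5D-3L covers "mobility, self-care, usual activities, pain/discomfort, and anxiety/depression" by self-report.
- *The criterion costs a known amount of power against an adjusted count.* With 80 per group, assumed arm use of 50% and conversion of 30% v 15%, the criterion has about 32% power (15% v 7.5%). A baseline-adjusted unassisted count with an assumed 1.5-stand difference, SD 4 and correlation 0.6 has about 84%. These are different assumed effects. The same 7.5-point excess of converters, at an assumed 8 stands each, is 0.075 × 8 = 0.6 stands. The standard error is 4 × √(1 − 0.6²) × √(2/80) ≈ 0.51, so power is about 22%, below the 32%. The comparison should not be used.

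It may also be said that an analysis plan can settle all this. It can settle how counts are handled by mode. But the article chose to state a criterion, and a later plan would have to replace or extend it.

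**Conclusion.** The point holds as a badly fixed rule for a secondary outcome. By logic alone, the single stated criterion cannot be met by anyone arm-free at baseline, does not score loss of arm-free standing, and can disagree with a count recorded in either mode. How often this happens depends on the baseline share of arm users and the number who change mode, neither of which the article gives. The power figures and mean shifts are therefore illustrations on assumed inputs. The documents do not show that the trial's conclusion on physical function will be wrong. They show that two readouts can conflict and that nothing says how to resolve it. The primary analysis is unaffected. This is a cheap improvement worth making.

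**What to change.** Using the mode and count already recorded:

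1. Replace the one-way criterion with a shift table of arm use at baseline and week 16, by group, showing both gain and loss of arm-free standing.
2. Define one ordered score: any unassisted performance ranks above any assisted performance, and within a mode more stands rank higher. This keeps the value the article places on giving up the arms. Rows 1, 2 and 4 of the first table then move up and row 3 moves down.
3. Compare groups on this score at week 16 with a rank or ordinal model adjusted for the baseline score.
4. State that assisted and unassisted counts are not treated as the same unit.

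The cost is a few sentences and no new data. The downside is an effect measure less direct than a difference in mean stands. Scoring assisted stands as zero is simpler, but it hides gains among arm users: three assisted rising to nine assisted would show no change.
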